## Participants

Informed consent will be obtained prior to randomization. To account for 25% attrition, we will recruit 102 participants with PD for this study. For group assignment, we will recruit PD patients (age ≥40, Hoehn & Yahr stage I–III) who report OFF-time, indicated by score ≥1 on UPDRS-IV item 4.3, i.e., time spent in the OFF-state. Their PD diagnosis (ICD-10 G20^*^) will be based on established criteria (64) and determined by a board-certified neurologist with training in movement disorders. Individuals must present asymmetric symptoms that include at least three of the cardinal signs of PD (rigidity, bradykinesia, tremor, postural instability) and must show clear symptomatic benefit from antiparkinsonian medications (65). Participants will be recruited from the Atlanta VA HCS Movement Disorders clinic and the Emory Movement Disorders clinic, as well as at local Parkinson-related support groups, educational meetings, and community events. We will also recruit via the Michael J. Fox Foundation FoxFinder web-based registry. Based on the ≈60% prevalence of reported OFF-times among participants in ongoing studies and our ability to recruit one in five contacted participants, we plan to initially contact 656 potential participants to reach the enrollment goal.

## Intervention

Fidelity will be monitored by the investigators via weekly reports from interventionists and monthly class visits of both investigators. Dose for intervention will be measured by the time spent in the class, e.g., one class is a dose of 90 min. Volume of the intervention is defined as frequency times duration, and therefore, the volume will be ~180 min/week for the Training phase and 90 min/week for the Maintenance phase. The intensity of exercise will be measured with heart rate monitors.

### Intervention Dose Determinations

Participants will have two phases of intervention. In the 3-month Training phase, participants will be assigned to 12 weeks of 20, biweekly (90-min) lessons. Participants will attend lessons during the maintenance phase at least 3×/month.

Fall incidence has been extremely rare over 10 years, but fall prevention is a critical concern. All assistants for both PDAE and WALK will be trained on PD-related posture problems, monitoring balance, and anticipating and preventing falls with a 2-h experiential workshop.

### Partnered Dance Aerobic Exercise

PDAE has been shown to improve motor function as measured by motor symptoms, balance, preferred, backward and fast gait, mobility, endurance, and QOL (51–56). It is an adapted form of Argentine tango, aka Adapted tango. People with PD partner an individual without PD, e.g., a trained caregiver, friend, or university student. The instructor and several trained assistants will carefully monitor all participants. Class sizes will consist of 10 or fewer pairs of participants with PD and partners to maximize safety. Participants with PD will dance the follower role only and will dance with new partners (individuals without PD) every 15 min, a widely practiced method considered by the dance teaching community to enhance learning. Participants will engage in partnering exercises on how to interpret motor goals through touch, exercises to develop understanding of temporal relationship of movement to music, novel step introduction, and connecting previously learned and novel step elements. Frequent repetition and musical stereotypes may foster implicit learning or muscle memory (i.e., motor learning or procedural memory that involves consolidating a specific motor task into memory through repetition). Participants will not be required to memorize specific step patterns but will learn new steps in each class.

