## Study Design

### Overall Study Design

The PAIRED trial builds upon more than 10 years of research investigating unique motor, cognitive, and symptomatic benefits of PDAE. The study will perform a two arm, randomized controlled trial comparing efficacy of PDAE vs. WALK for improving OFF-time and visuospatial cognition among individuals with PD who report OFF-time. We will randomize *n* = 82 participants equally to 16 months of PDAE (*n* = 41) or to walking as aerobic exercise WALK (*n* = 41) in blocks of two to reduce variability within treatment conditions. Participants will be stratified by sex and Hoehn & Yahr (H&Y) staging (I, II, or III). The 16-month intervention period will consist of Training (3 months) and Maintenance (13 months) phases. In Training, participants will complete 20 biweekly 90-min sessions. In Maintenance, participants will complete 90-min weekly sessions. To evaluate SNc neurodegeneration over the observation period, we will image patients at study entry and 16-month follow-up using fMRI sequences. We will compare SNc volume and iron accumulation estimates in PDAE vs. WALK to assess whether PDAE is more neuroprotective.

Participants will be assessed at baseline, 3 months (immediately post-Training), and at 16 months (immediately post-Maintenance) for OFF-times, cognition, and neuroprotection, as evaluated in the SNc. At a standardized time of day, participants will be tested on all outcome measures at least 12 h after their last dose of antiparkinsonian medications. Furthermore, participants will keep an OFF-time diary to corroborate MDS-UPDRS-IV assessments. Participants will be ON medications during intervention. In addition to the primary motor and cognitive outcome measures, participants will be tested on secondary behavioral motor and cardiovascular and cognitive outcomes. Participants will undergo NM-MRI and fMRI scans at baseline and 3 and 16 months assessments to investigate mechanisms by which cognitive benefits have been obtained and replicated by PDAE and whether PDAE vs. WALK is neuroprotective, as exhibited by slowed rate of NM loss and iron accumulation and increased functional connectivity with spatial cognitive areas.

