### Walking Aerobic Exercise

Participants in WALK will receive equivalent dose, volume, frequency, intensity, and duration of exercise to the PDAE group. They will receive equal contact and monitoring from study staff. WALK participants will report to the same facility and interact with the same interventionist and assistants. They will participate in sessions focused on at least 60 min of walking with breaks *ad libitum* and half hour balance and stretching. We have a designated safe and non-cluttered area for walking. WALK will also take place in groups, with research volunteers and assistants to ensure that PDAE and WALK participants both receive a socially engaging intervention.

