### Analyses

#### Aim 1

We will analyze the primary study outcome with a mixed effect model (treating subject as random) with between-subjects effect of group (PDAE vs. WALK) and within-subjects timepoints (study entry, 3-month follow-up, 16-month follow-up) plus their interaction term. If the interaction term is significant, we will test differences between PDAE and WALK in the change from baseline to 3 months and from baseline to 16 months using Holm's procedure to control for multiple testing. We will consider covariates sex and H&Y staging (<III, ≥III) in the analyses.

#### Aim 2

The secondary outcome Corsi Blocks Score will be analyzed using a similar mixed effects model.

#### Aim 3

We will use similar analyses. We will use mixed effects model except that it will be a two-group (PDAE vs. WALK) and a two-level variable for time (study entry vs. 16-month follow-up).

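### Both arms are treated in groups, but the primary model and the power calculation treat participants as independent; if outcomes correlate within class, standard errors are too small and the stated power is too high

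*Protocol article*

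**What the plan says.** All references are to the protocol article.

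- **Randomisation** (Overall Study Design): individual participants are allocated 1:1, 41 per arm, to 16 months of treatment.
- **Delivery of PDAE** (Partnered Dance Aerobic Exercise): "Class sizes will consist of 10 or fewer pairs of participants with PD and partners". Dance partners rotate every 15 minutes.
- **Delivery of WALK** (Walking Aerobic Exercise): "WALK will also take place in groups, with research volunteers and assistants". No group size is stated. "WALK participants will report to the same facility and interact with the same interventionist and assistants".
- **Primary model** (Analyses, Aim 1): "We will analyze the primary study outcome with a mixed effect model (treating subject as random", with fixed effects for group, time and their interaction. Sex and Hoehn & Yahr stage are the only covariates named. Aims 2 and 3 use similar models.
- **Testing order** (Analyses, Aim 1): "If the interaction term is significant, we will test differences between PDAE and WALK in the change" from baseline to 3 and to 16 months, with Holm's procedure.
- **Power** (Power and Sample Size for the Primary Outcome): d = 0.7 with 41 completers per group gives 81% at alpha 0.025 and 88% at alpha 0.05. No ICC or design effect appears.

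**The concern.** When people are treated together, their outcomes can become correlated after randomisation through class composition, schedule, cohesion or the way a class progresses. The trial's own rationale makes this plausible. The Discussion names psychosocial engagement as a possible route to less OFF-time and expects social support and touch to help both OFF-time and cognition.

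A subject random effect covers only the correlation among one person's repeated measurements. It does not cover correlation among classmates. If that correlation is positive, the between-arm contrast varies more than the model believes. Confidence intervals are then too narrow, the tests at 0.025 and 0.05 reject too often under the null, and power computed from 82 independent participants is too high.

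The random-effects structure is written out in the article, so this is a stated choice rather than a detail left to an analysis plan that is not shown.

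**Working it through.** **Inputs from the document:** 41 completers per arm, d = 0.7, alpha 0.025 and 0.05, a ceiling of 10 PDAE participants per class.

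**Assumed, because the document is silent:** ICC of 0 to 0.05 for change in the primary outcome; WALK groups of the same size as PDAE classes; stable class membership.

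**Step 1: reproduce the stated power.** For two independent groups the noncentrality is 0.7 × √(41/2) = 3.169. The two-sided noncentral t test with 80 df gives 81.0% at alpha 0.025 and 87.9% at alpha 0.05, matching the stated 81% and 88%. One-sided tests give 87.9% and 93.3% and do not match. The stated power therefore assumes a design effect of 1.

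**Step 2: single tests and power under clustering.** With m per class:

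- design effect DE = 1 + (m − 1) × ICC
- actual level of the unadjusted test = 2 × [1 − Φ(z/√DE)], with z = 2.241 for 0.025 and 1.960 for 0.05
- power with a correct standard error: noncentral t with 41/DE effective participants per arm (design effect only)

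| ICC (m = 10) | DE | Actual level, nominal 0.025 / 0.05 | Power at alpha 0.025 / 0.05 |
|---|---|---|---|
| 0 | 1.00 | 0.025 / 0.050 | 81% / 88% |
| 0.01 | 1.09 | 0.032 / 0.060 | 77% / 85% |
| 0.02 | 1.18 | 0.039 / 0.071 | 73% / 82% |
| 0.05 | 1.45 | 0.063 / 0.104 | 63% / 73% |

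With m = 5 the levels are 0.031 / 0.059 at ICC 0.02 and 0.041 / 0.074 at ICC 0.05.

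**Step 3: familywise error of the planned sequence.** This was simulated with 20,000 runs, 41 per arm, classes nested in both arms and an assumed correlation of 0.5 between the 3- and 16-month changes. The interaction test was represented by a joint test of the two changes. The layout with about 10 per class was 10, 10, 10 and 11, so one class is one over the stated ceiling.

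| ICC | Holm alone, about 10 per class | Interaction test, then Holm, about 10 per class | Interaction test, then Holm, about 5 per class |
|---|---|---|---|
| 0 | 0.045 | 0.035 | 0.033 |
| 0.01 | 0.057 | 0.045 | 0.039 |
| 0.02 | 0.071 | 0.057 | 0.046 |
| 0.05 | 0.116 | 0.098 | 0.060 |

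The simulated single-test levels at ICC 0.05 with about 10 per class were 0.064 and 0.108, in line with Step 2.

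**Step 4: degrees of freedom.** A ceiling of 10 means at least five PDAE classes for 41 people. Five classes per arm leave 2 × (5 − 1) = 8 class-level df, and the critical t at alpha 0.025 rises from 2.284 (80 df) to 2.752. At ICC 0.02 and m = 10, the effective number per arm is 41/1.18 = 34.7 and the noncentrality is 0.7 × √(34.7/2) = 2.92. Power at alpha 0.025 is then about 59%, against 73% from the design effect alone. With m = 8, closer to the average of 41/5 = 8.2, DE is 1.14 and power is about 60%. Even at ICC 0, 8 df gives about 66%.

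**The case against.** A reader might infer that the classes are of fixed size and that the type I error of this trial does exceed its Holm levels. The document supports neither reading. Ten is a ceiling, it applies to PDAE only, and no WALK group size is given. Inflation requires a positive class-level ICC, which the document does not report; at ICC 0 there is none.

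Other points also stand against a strong reading:

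- The interaction must be significant before the 3- and 16-month contrasts are tested. This keeps the simulated familywise error under 0.05 at ICC 0.01 with about 10 per class and at ICC 0.02 with about 5 per class.
- The same interventionist and assistants serve both arms, so an instructor effect is crossed with arm rather than nested in it. Partner rotation spreads partner effects, and a blinded rater scores the primary outcome. These features limit clustering, but none removes correlation that arises from sharing a class.
- Closed cohorts are not described, and Maintenance requires attendance at least three times a month. If people move between classes, the correlation at 16 months is weaker and a simple nested effect describes it less well.
- The remedy costs more than an extra model term suggests, because few classes mean few degrees of freedom.

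One could add that a condensed article may leave a clustering analysis to a fuller document. That has less force here: the article states the model's random effect, and its power figures assume independence.

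**Conclusion.** The point holds as a conditional one. The document states group delivery in both arms, a model with subject as the only random effect, and power that reproduces only under independence. It follows that any positive within-class correlation makes the planned standard errors too small and the stated power too high.

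The size cannot be fixed from the document. Over the assumed ICC range of 0 to 0.05 it runs from no effect to roughly a doubling of the nominal levels for classes of 10 (0.063 and 0.104). For the whole testing sequence, familywise error passes 0.05 at an ICC somewhere between 0.01 and 0.02 with about 10 per class, and between 0.02 and 0.05 with about 5. These figures rest on stable classes and on WALK groups like the PDAE classes; smaller or changing groups bring them down. The plan should be amended, but inflation of the error rate has not been demonstrated.

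**What to change.** 1. Record the class of each participant in both arms, separately for Training and Maintenance.
2. Add a class random effect nested in arm to the Aim 1 to 3 models, with Kenward-Roger or Satterthwaite degrees of freedom. At minimum, prespecify this as a sensitivity analysis, particularly if class membership changes between phases. If the class variance is estimated at zero, the model reduces to the planned one.
3. Restate the power over an explicit ICC range, including the loss of degrees of freedom. On the design effect alone, keeping the stated power with 10 per class would take 2 × 49 = 98 completers at ICC 0.02 (41 × 1.18 = 48.4) or 2 × 60 = 120 at ICC 0.05 (41 × 1.45 = 59.5), instead of 82.

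The data cost is one variable per phase, which may be hard to reconstruct later if it is not recorded. The statistical cost is wider intervals and a less favourable stated power. At alpha 0.025 and ICC 0.02, power is about 73% from the design effect alone and about 59% if only 8 class-level degrees of freedom are available. A small positive variance estimate would bring some of that loss even where true clustering is negligible, which is the main argument for the sensitivity-analysis form.

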### Walking Aerobic Exercise

Participants in WALK will receive equivalent dose, volume, frequency, intensity, and duration of exercise to the PDAE group. They will receive equal contact and monitoring from study staff. WALK participants will report to the same facility and interact with the same interventionist and assistants. They will participate in sessions focused on at least 60 min of walking with breaks *ad libitum* and half hour balance and stretching. We have a designated safe and non-cluttered area for walking. WALK will also take place in groups, with research volunteers and assistants to ensure that PDAE and WALK participants both receive a socially engaging intervention.

## Pretest and Posttest Procedure Descriptions

Participants will be characterized for general health with a questionnaire at the first assessment. For blinded ratings, procedures will be videotaped and rated by research assistants. Through all assessments, to avoid fatigue, participants will have breaks *ad libitum* and will be offered snacks and water. The MDS-UPDRS parts I–IV will be administered to participants at all evaluations (1-week pretest, 1-week posttest, and 13-month posttest), by a qualified, MDS-certified and blinded rater. In addition to having reported OFF-time, participants must have a score >17 on the MoCA to screen out overt dementia (66). We will screen for depression with the Beck Depression Inventory-II (BDI-II), recommended for individuals with PD, with a cutoff of 18 (67). If participants are excluded for depression but receive treatment, they may be rescreened and considered for recruitment.

## Evaluations

### Self-Administered Psychosocial Questionnaires

To measure psychosocial impact of the social/touch human interactions inherent to partnered dance exercise, participants will have a week before each visit to complete questionnaires, i.e., Beck Depression Index II, the Composite Physical Function index. (68), the Physical Activity Scale for the Elderly, the PD Questionnaire-39 [patients have previously improved on this test as a result of PDAE (52)], and Short Form 12 Health Survey. We will also administer the five-item Satisfaction with Life Scale, which is valid in people with PD (69). As an exploratory measure, we will administer the Multidimensional Scale of Perceived Social Support (MSPSS) (70). The MSPSS aims to determine how social support factors are perceived by individuals, with three subscales to evaluate support by family, friends, and significant others. We will administer the Exit (Satisfaction) Questionnaire at 3- and 16-month assessments to survey satisfaction with Training and Maintenance phases of PDAE and WALK interventions and to elicit recommendations.

### Disease Severity

A blinded MDS-certified rater will administer the MDS-UPDRS parts I–IV at all evaluations. We will videotape Motor Subscale III. The primary outcome, the MDS-UPDRS-IV score (71), measures MRMF including dyskinesias, OFF-time, functional impact and complexity of fluctuations, and dystonia. We will administer a monthly OFF-state diary (72) for corroboration.

### Neuropsychological Assessment

Neuropsychological assessments will include the reverse Corsi blocks (73), a test of spatial function. The Brooks spatial memory and the Benton's judgment of line orientation will be administered as secondary, corroborative outcomes. We expect the interventions to benefit other aspects of cognition: attention/working memory, executive function, and visuospatial functions. Spatial cognition, attention, and executive function deficits result in impaired mobility, dual tasking problems, postural-gait disturbances, and ultimately falls (17, 18). The Trail Making Test and the Tower of London, both tests of executive function, will also be administered. Standard scores of simple conditions (using the timed motor responses) will take pure motor slowing into account. We will use different test versions at each time point to address practice effects. Analysis of the neuropsychological assessment data will be performed by a blinded analyst.

### Motor/Cardiovascular Assessments

#### Endurance: Six-Minute Walk Test

PDAE-mediated improvements in PD patients in 6-Min Walk Test (6MWT) performance have been demonstrated previously (53).

#### Gait Objective

Spatiotemporal parameters including velocity, stride length, stance percent, velocity variability, and other variables of preferred, backward, and fast-as-possible walking will be assessed by a 6-m computerized GAITRite walkway (CIR Systems, Inc. Havertown, PA, USA). We are examining backward walking because it is frequently practiced in PDAE and is more likely to be impaired earlier in the disease than forward walking and is more sensitive to change over time (74). We are examining fast as possible walking because it is sensitive to the effects of PDAE (53).

#### Balance

The Mini BEST test (75) and dynamic gait index (76).

#### Mobility and Dual Tasking

Single and Dual Timed Up and Go test (TUG) and four-square step test (77).

#### Cardiovascular Fitness Assessment

Participants will perform a submaximal exercise test on a cycle ergometer at baseline and 3- and 16-month assessments, per Young Men's Christian Association's (YMCA) submaximal test protocol. This submaximal test can estimate the participant's VO_2_ max and initial fitness level. This test uses a method in which heart rate (HR) workload values are obtained at 2–4 points and extrapolated to predict workload at the estimated maximum HR (e.g., 220-age). VO_2_ max is then calculated from the predicted maximum workload. A blinded assessor will ask participants to ride a stationary bicycle for four, 3-min stages. The first stage will be a warm-up at 50 revolutions per minute (rpm) at a power level of 25 W. We will continuously monitor HR and will not exceed 85% of age-predicted maximum HR. We will plot the average HR during the final 30 s of the second and third minutes against the workload. We will choose 3-min trial workloads based on participants' HR at the end of the warm-up. The fourth 3-min stage is the cooling down at the end of the test. A screening protocol based on a cardiovascular reserve test is more suitable for screening older adults (78).

#### Scanning/Neuroimaging

Participants will return for scanning within 3–4 days of clinical measures testing. We will examine participants in the OFF-state.

#### MRI Approach: Pulse Sequences and Standard Image Processing

NM-MRI, R2^*^, T_1_ MPRAGE, and T2^*^-weighted blood-oxygen-level-dependent (BOLD) fMRI data will be acquired using a Siemens Prisma-Fit 3T MRI scanner with a 64-channel receive-only head coil in a protocol with total scan time of 1 h. The NM-MRI sequence is the custom protocol developed by our group (41, 44). We will acquire NM-MRI data using a 2-D gradient echo sequence with a reduced flip-angle magnetization transfer preparation pulse (300°, 1.2 kHz off-resonance, 10 ms duration), TE/TR = 3.10/354, 15 contiguous slices, 416 × 512 imaging matrix, voxel size 0.39 × 0.39 × 3 mm^3^, seven measurements, flip angle = 40°, 470 Hz/pixel receiver bandwidth, and scan time of 17 min and 12 s (79). A blinded MRI analyst will carry out image processing to determine SNc volume using an automated approach previously shown to have high scan–rescan reproducibility (41, 79) and acquire R2^*^ data using conventional multiecho gradient echo sequence with four echoes spaced equally (see citation for parameters) (80). We will measure R2^*^ in the NM-MRI-defined SNc using a published image processing and analysis method (44, 45). We will use NM-MRI to delineate SNc and T2-weighted (iron-sensitive) MRI to delineate SNr. We will use an NM-MRI SNc population mask and a T2-weighted SNr population mask using data from a group of healthy controls (45) to select SNc and SNr ROIs with no operator-dependent steps (45).

